
**Table 3 T3:** **Neonatal acute kidney injury KDIGO classification (21)**.

Stage	Serum creatinine	Urine output
0	No change in sCr *or* rise <0.3 mg/dl	> 1 ml/kg/h
1	sCr rise ≥0.3 mg/dl within 48 h or sCr rise ≥1.5–1.9× reference sCr^a^ within 7 days	> 0.5 ml/kg/h and ≤ 1 ml/kg/h
2	sCr rise ≥2–2.9× reference sCr^a^	>0.3 ml/kg/h and ≤ 0.5 ml/kg/h
3	sCr rise ≥3× reference SCr^a^ or sCr ≥2.5 mg/dl^b^ or receipt of dialysis	≤ 0.3 ml/kg/h

Differences between the proposed neonatal AKI definition and KDIGO include:

*^a^Reference sCr will be defined as the lowest previous sCr value*.

*^b^sCr value of 2.5 mg/dl represents less than 10 ml/min/1.73m^2^*.

Similarly, fluid overload has been identified as a major risk factor for morbidity and mortality in adult and pediatric patients with AKI (24, 25), but has not been fully examined in the neonatal population. As with the study of sCr in this group, the unique physiology of neonates, especially premature and low-birth weight infants, creates challenges for applying concepts developed in older patients to this special group. In the first few days after birth, healthy term infants will lose around 7% of their weight. Depending on the amount of fluid provision, ambient temperature and humidity, gestational age, and kidney function, infants admitted to the NICU will have different amounts of weight losses due to changes in fluid balance over the first weeks of life (26).

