The primary hypothesis of AWAKEN is that neonatal AKI is common and associated with increased mortality, longer length of NICU stay and higher discharge serum creatinine, even after controlling for severity of illness, interventions and demographics. The two secondary hypotheses of AWAKEN include (1) maternal and infant risk factors can predict AKI and (2) fluid balance is associated with clinical outcomes (Table 4). Ultimately, the NKC will be positioned to test and validate the proposed neonatal AKI definition and compare it with other AKI definitions to determine which definition is the most accurate. We anticipate that the AWAKEN study can validate these hypotheses because of the large sample size and rich data set. This multicenter study will also uncover variations in practice patterns among NICUs in relation to fluid provision, renal function monitoring, bedside identification of AKI and AKI risk factors, and the involvement of pediatric nephrologists during inpatient hospitalization. Moreover, AWAKEN will provide important information regarding critical time and data points necessary to build a meaningful prospective study in the future.

**Table 4 T4:** **Primary hypotheses of AWAKEN**.

*Hypothesis #1*: Neonatal AKI is associated with short-term risk, even when adjusted for gestational age at birth, birthweight, 5 min Apgar score, congenital renal anomalies, and severity of illness score	Survival of infants to discharge or 120 days of age (or to 36 weeks’ postmenstrual age in infants born preterm) is less likely in babies with the diagnosis of AKI
	Length of stay is longer in infants with neonatal AKI
	Discharge serum creatinine is higher in infants with neonatal AKI
*Hypothesis #2*: Maternal and infant risk factors predict AKI	
*Hypothesis #3*: Fluid balance during the first week after birth is associated with short-term risk	Survival of infants to discharge or 120 days of age (or to 36 weeks’ postmenstrual age in infants born preterm) is less likely in babies with excessive fluid intake compared to output
	Changes in weight are a better indication of fluid balance, especially in the preterm population, than difference between fluid intake and measured output
	Length of stay is longer in infants with neonatal AKI
	Pulmonary outcomes, as measured by time to extubation and development of bronchopulmonary dysplasia, are worse in infants with evidence of fluid overload
	Discharge serum creatinine is higher in infants with fluid overload

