### Setting

Twenty-four level 2–4 NICUs in the United States (*n* = 20), Canada (*n* = 2), India (*n* = 1), and Australia (*n* = 1). A broad description of each institution is listed in Table 2, including the number of neonates enrolled in AWAKEN, the percentage of neonates born at that institution and the type of assay used to measure serum creatinine.

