## Discussion

The AWAKEN study created the largest cohort of neonates assembled to date for exploring AKI in this vulnerable patient population. Across the 24 centers with high acuity NICUs distributed across 3 continents and 4 countries, we screened 4273 and enrolled 2162 newborns during the 3 months’ time-period. As demonstrated in Table 2, the institutions represented in the AWAKEN study include academic medical centers with diverse referral patterns, volumes of patients and creatinine assay methods. By collecting detailed demographic information on these babies, the NKC has created a rich database with which we will be able to describe the prevalence of neonatal AKI in different ethnic, racial, and geographic populations. Analyses can be performed based on birthweight, gestational age, and other criteria. Daily weights can be assessed as a surrogate for “fluid balance” in the first week after birth in ELBW neonates given the difficulty in accurately determining fluid status based solely on intake and measurable output. Although data points were chosen based on relatedness to renal function and injury, the database will be a source of carefully collected information on NICU patients that may be used to compare practices across sites and investigate various best practices in this population, including strategies for fluid provision.

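### The covariate list stated for Hypothesis #1 omits centre, and with it creatinine assay, so between-centre differences can bias the AKI associations in either direction

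*Protocol article*

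**What the plan says.** Table 4 (The AWAKEN Study) gives Hypothesis #1 three outcomes: survival, length of stay and discharge creatinine. The association with AKI is to hold "even when adjusted for gestational age at birth, birthweight, 5 min Apgar score, congenital renal anomalies, and severity of illness score". The paragraph before the table describes the adjustment differently: "even after controlling for severity of illness, interventions and demographics". Neither description includes centre or assay. The Analyses section names no model and no handling of centre.

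Creatinine is on both sides of the comparison. In Table 3, AKI can be reached by an absolute change, "sCr rise ≥0.3 mg/dl within 48 h", by a ratio to a reference value, by a level of 2.5 mg/dl (stage 3), by dialysis, or by urine output. On the reference value: "Reference sCr will be defined as the lowest previous sCr value". One of the outcomes is also a creatinine level: "Discharge serum creatinine is higher in infants with neonatal AKI".

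The Setting section points to Table 2 for each site's enrolment, inborn share and "the type of assay used to measure serum creatinine". The Discussion presents the sites as having "diverse referral patterns, volumes of patients and creatinine assay methods". The article also expects renal function monitoring to vary between units, and lists as a limitation that the treating neonatologist decides when creatinine is measured.

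**The concern.** In a pooled model without a centre term, the AKI coefficient mixes two comparisons: infants with and without AKI in the same unit, and units with more recorded AKI against units with less. The second is open to confounding by anything that differs between units and affects both recorded AKI and the outcome. The article itself names candidates: how often creatinine is measured, which infants are referred in, and which assay is used. The five listed covariates are infant characteristics. They may capture part of the case mix, but they do not capture sampling practice or assay.

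Assay bears most directly on discharge creatinine, because a method that reads higher shifts that outcome itself. For mortality and length of stay it acts only through who is classified as having AKI; there, local practice and case mix are the stronger reasons for a centre term.

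The two covariate descriptions raise a smaller, related matter. The text adjusts for interventions and Table 4 lists none. Receipt of dialysis is part of the stage 3 definition, so an intervention covariate with no time restriction could adjust for part of the exposure or its consequences.

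**Working it through.** **Inputs from the article.** Table 2 gives enrolment, inborn share and assay for 24 centres. The counts sum to 2163; the Figure 2 legend states 2162, one infant fewer, which is immaterial here.

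| Assay | Centres | Infants | Share of 2163 |
|---|---|---|---|
| Enzymatic | 16 | 1616 | 74.7% |
| Jaffe | 7 | 37+58+69+67+59+93+101 = 484 | 22.4% |
| Both | 1 | 63 | 2.9% |

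Inborn share runs from 0% to 100% and enrolment from 37 to 192. Weighted by enrolment, inborn share is similar at Jaffe (58%) and enzymatic (56%) sites, so assay is not a simple proxy for referral pattern.

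**Effect of an offset on AKI classification.** Suppose one assay reads higher by a constant *b* (an assumption; the article gives no offset).

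- Absolute rise: (peak + *b*) − (reference + *b*) = peak − reference. The offset cancels.
- Ratio: (peak + *b*)/(reference + *b*) shrinks. For a rise from 0.40 to 0.62 mg/dl:
  - *b* = 0: 0.62/0.40 = 1.55, stage 1
  - *b* = 0.1: 0.72/0.50 = 1.44, not AKI by creatinine
  - *b* = 0.2: 0.82/0.60 = 1.37, not AKI by creatinine
  - The rise of 0.22 is below 0.3, so the absolute criterion does not recover the case.
- Level of 2.5 mg/dl: easier to reach where the assay reads higher.

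The effects run in different directions. Under the ratio criterion, sites with higher discharge creatinine would record less AKI, which pulls the discharge-creatinine association towards the null or below it.

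**Effect on discharge creatinine.** With no true AKI effect, the spurious AKI-minus-no-AKI difference is

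offset × [P(Jaffe | AKI) − P(Jaffe | no AKI)].

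The Jaffe share among single-assay sites is 484/(484+1616) = 0.230. Offsets of 0.1 to 0.3 mg/dl (Jaffe higher) and AKI prevalences by assay are assumptions, centred on the article's figure of about 30%.

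| AKI at Jaffe / enzymatic | P(Jaffe given AKI) − P(Jaffe given no AKI) | Spurious difference, mg/dl |
|---|---|---|
| 30% / 30% | 0 | 0 |
| 40% / 27% | 0.307 − 0.198 = 0.110 | +0.011 to +0.033 |
| 20% / 33% | 0.154 − 0.263 = −0.110 | −0.011 to −0.033 |
| 40% / 13% (extreme) | 0.480 − 0.171 = 0.308 | +0.031 to +0.093 |
| 13% / 40% (extreme) | 0.089 − 0.303 = −0.214 | −0.021 to −0.064 |

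**Effect on mortality.** A simulation used the Table 2 centre sizes, no within-centre AKI effect, and assumed values of 30% AKI, about 5% mortality and between-centre SDs of 0.3 to 0.6 on the logit scale for each. It included no infant-level covariates. The odds ratio obtained when centre is ignored depends on the correlation between centre AKI rate and centre mortality:

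- correlation 0: median 1.00
- correlation +0.5: median 1.04 to 1.16
- correlation −0.5: median 0.86 to 0.96

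**The case against.** Table 4 is a table of hypotheses in a condensed article, not a model specification. The full protocol or analysis plan is not shown, and a centre term may be in it. This stands as a limit: one cannot say that the analysis will ignore centre. It does not remove the point, because five specific covariates are named for the primary hypothesis and the published list should agree with whatever is fitted. For Hypotheses #2 and #3 no adjustment list is stated, so nothing there is wrong as written.

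It is also fair to object that AKI is judged against each infant's own earlier value, which protects the 0.3 mg/dl criterion from a constant offset, and that urine output offers a route to diagnosis without creatinine.

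Three stronger readings are tempting and not supported:

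- **Site differences will be read as AKI effects in every association.** The article gives no AKI rate, mortality or creatinine level by centre or assay. The bias could be nil or of either sign.
- **The intervals for Hypothesis #1 are too narrow by a known factor.** A design effect computed from centre size applies to pooled incidence and needs an assumed intraclass correlation. It does not carry over to an adjusted comparison in which AKI varies within centres.
- **Geographic comparisons are invalid.** The Discussion offers only to "describe the prevalence of neonatal AKI in different ethnic, racial, and geographic populations". India and Australia are one Jaffe centre each, so labelling them as single-centre results would help readers, but that is presentation.

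Nor does the article say that its interventions are those given after AKI; resuscitation data, for example, are also collected.

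**Conclusion.** The point holds in a limited form. The adjustment set stated for Hypothesis #1 omits centre and therefore assay, while the same article documents between-site differences in assay, referral and monitoring that plausibly affect both recorded AKI and the outcomes. The omission permits bias in either direction, most directly for discharge creatinine. Its size cannot be derived from the article: the illustrative figures rest on assumed offsets, assumed AKI prevalences by assay and assumed between-centre variation, and they include zero. The mismatch between the two covariate descriptions needs no assumption. Both deserve correction before analysis because the remedy is cheap and centre is already recorded; neither shows that the study's conclusions would be wrong.

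**What to change.** 1. Add centre to the Hypothesis #1 models, by random intercept or stratification, with standard errors that allow for clustering. Use the same approach in the other association models. Stratification gives the purely within-centre comparison; a random intercept keeps some between-centre information, so comparing the two is a useful check.
2. Examine assay separately, either by repeating the analysis in the 16 enzymatic sites (1616 infants, leaving out the mixed site as well as the Jaffe sites) or as a between-centre covariate under a random intercept. Do not enter it as a main effect beside fixed or stratified centre effects: it is constant within 23 of 24 centres and cannot be estimated there. The article does not describe assay type being recorded per creatinine value, so the fix should not depend on it at the mixed site.
3. State one covariate list in both the text and Table 4. If intervention covariates are kept, limit them to those preceding AKI onset.

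The cost is wording, a little more analysis and somewhat wider intervals. The enzymatic-only analysis gives up about a quarter of the cohort (547 of 2163, 25.3%), which is acceptable for a sensitivity analysis. No new data are needed.

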## Methods and Analysis

### Design

Assessment of Worldwide Acute Kidney injury Epidemiology in Neonates is a multi-center, international, retrospective cohort study. All neonates who fulfilled the inclusion and exclusion criteria at each of the 24 participating centers from January 1, 2014 until March 31, 2014 were enrolled (Figure 2). Detailed data collection continued until one of the following endpoints was reached: discharge to home, transfer to another facility or out of the NICU for escalating or convalescent care, death or 120 days of age. Limited information was collected between 120 days and final disposition. The study was registered at ClinicalTrials.gov (https://clinicaltrials.gov/ct2/show/NCT02443389?term=kidney+awaken&rank=1).

**Figure 2 F2:**
[figure not shown]
**Of the 4273 NICU admissions at the 24 participating institutions during the period 1/1/14–3/31/14, 2162 patients were enrolled**. The majority of those not included did not receive at least 48 h of IV hydration and/or nutrition. The second most common reason for exclusion was admission to the NICU at greater than 14 days of age. Subjects may have been excluded for more than one reason and may be counted more than once in the “not enrolled” numbers.

### Setting

Twenty-four level 2–4 NICUs in the United States (*n* = 20), Canada (*n* = 2), India (*n* = 1), and Australia (*n* = 1). A broad description of each institution is listed in Table 2, including the number of neonates enrolled in AWAKEN, the percentage of neonates born at that institution and the type of assay used to measure serum creatinine.

### Inclusion and Exclusion Criteria

All infants admitted from January 1, 2014 to March 31, 2014 who were ≤14 days of age and received at least 48 h of intravenous (IV) fluids as their primary source of hydration or nutrition (Table 5). Neonates who received IV fluids given solely for the administration of medications or line flushes were not included. The inclusion criteria were designed to capture sick neonates at significant risk for AKI and those who had an expected hospitalization of at least 48 h. Infants receiving routine care in the newborn nursery were not included in this study. The exclusion criteria were designed to omit patients with a limited hospitalization in the NICU or who had significant incomplete data particularly in the first 2 weeks of life. This exclusion is based on the belief that the first 2 weeks of life encompass a critical at-risk time for AKI. Because of the variable center-specific practice patterns regarding newborns with congenital heart disease requiring surgical repair (i.e., transfer to the PICU for post-operative care) and because these infants have been the subject of a number of previous AKI studies, neonates who required cardiac surgery within 7 days of birth were excluded. Infants with isolated ventricular septal defect, atrial septal defect, or patent ductus arteriosus were included unless they were transferred out of the NICU <7 days for surgical repair. Premature infants who remained in the NICU for ≥7 days to gain weight and grow in preparation for surgery were also included.

**Table 5 T5:** **Inclusion and exclusion criteria**.

Inclusion criteria	Exclusion criteria
Admitted to participating NICU between 1/1/14 and 3/31/14 ≥48 h of IV fluids	Age greater than 14 days at admission Congenital heart disease with surgery <7 days of life Lethal chromosomal anomaly; including trisomy 13, 18 and anencephaly Neonatal mortality <48 h

All neonates admitted to the participating NICUs were screened for inclusion criteria. Demographic data including sex, self-reported ethnicity, race, date of birth, and date of NICU admission were collected for all neonates (Supplementary Materials – Data Sheet 1 – Screening Form). Date of birth was required as an “anchor” for the database format and the generation of the appropriate daily and weekly forms and was designated as “day 1.”

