#### Discharge Data

Disposition of the infant at the end of the data collection period (“status” – discharged home prior to 120 days, still in the NICU at ≥120 days, transferred to another facility for convalescent care, transferred to another facility for escalation of care or died on or prior to 120 days), growth parameters, discharge medications if kidney related (urinary tract infection prophylaxis, antihypertensive medications and diuretics), and discharge diagnoses. Detailed information about kidney diagnoses (congenital abnormalities, episodes of AKI and need for nephrology consults) and renal replacement therapy provided were collected.

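### Infants born without kidney function are not excluded and would be classed as stage 3 AKI, and adjusting for renal anomalies as one pooled category would leave most of the resulting bias

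*Protocol article*

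**What the plan says.** Four parts of the protocol article bear on this point.

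- **Eligibility (Inclusion and Exclusion Criteria, Table 5).** Infants qualify if they "received at least 48 h of intravenous (IV) fluids as their primary source of hydration or nutrition". Two exclusions concern expected or early death: "Lethal chromosomal anomaly; including trisomy 13, 18 and anencephaly" and "Neonatal mortality <48 h". No kidney malformation is named.
- **AKI definition (The AWAKEN Study, Table 3).** Stage 3 is reached by a threefold creatinine rise, by a creatinine of at least 2.5 mg/dl, "or receipt of dialysis", or by urine output of 0.3 ml/kg/h or less. Kidney failure present from birth is not treated differently.
- **Primary hypothesis (Table 4).** AKI is to be associated with short-term risk "even when adjusted for gestational age at birth, birthweight, 5 min Apgar score, congenital renal anomalies, and severity of illness score". The first component is that survival "is less likely in babies with the diagnosis of AKI"; the other two are length of stay and discharge creatinine.
- **Data (Discharge Data).** The forms hold "Detailed information about kidney diagnoses (congenital abnormalities, episodes of AKI and need for nephrology consults", together with any renal replacement therapy.

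**The concern.** Aim 1 asks whether the neonatal KDIGO definition is independently associated with death and the other short-term outcomes. An infant without working kidneys meets stage 3 because of the malformation, and a high risk of death follows from the same malformation. Such an infant adds to the AKI-and-died cell without showing whether acute injury carries risk.

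The listed covariate is the plan's safeguard. It works only if infants with and without AKI are comparable within its levels. Under Table 3, essentially every infant with congenital kidney failure is AKI-positive. If severe and mild malformations share one category, AKI status separates the severe from the mild, and the malformation's mortality is credited to AKI. The error favours the hypothesis under test, and it would also enter the comparison of AKI definitions.

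**Working it through.** **Inputs from the article.** Enrolled: 2,162 (the Table 2 site counts sum to 2,163, a one-infant difference that does not matter here). AKI prevalence: about 30%. Mortality: 14% with AKI and 4% without, the Table 1 row with the smallest computable odds ratio.

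**Inputs assumed, because the article gives none.** Number of infants with congenital kidney failure, k: 5, 10 or 20. Number with a mild anomaly, m: 0, 40, 60 or 100, with the same AKI prevalence and mortality as the remaining infants.

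**Step 1, base odds ratio.** AKI infants: 0.30 × 2,162 = 648.6, of whom 0.14 × 648.6 = 90.8 die and 557.8 survive. Non-AKI infants: 1,513.4, of whom 60.5 die and 1,452.9 survive. The odds ratio is (0.14 × 0.96)/(0.86 × 0.04) = 3.91.

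**Step 2, no adjustment, all k infants die.** The odds ratio is multiplied by 1 + k/90.8. For k = 10 this is 1.11, so 3.91 becomes 4.34 (+11%).

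**Step 3, adjustment by one yes/no anomaly flag (Mantel-Haenszel), k = 10, m = 40.** Cells are AKI died, AKI survived, no-AKI died, no-AKI survived.
- Flagged stratum (n = 50): 11.68, 10.32, 1.12, 26.88.
- Unflagged stratum (n = 2,122): 89.12, 547.48, 59.42, 1,425.98.
- Numerator: 89.12 × 1,425.98/2,122 + 11.68 × 26.88/50 = 59.89 + 6.28 = 66.17.
- Denominator: 547.48 × 59.42/2,122 + 10.32 × 1.12/50 = 15.33 + 0.23 = 15.56.
- Adjusted odds ratio: 66.17/15.56 = 4.25, or +8.8% against +11.0% unadjusted. With m = 100 it is 4.30 (+10.1%).

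The pooled flag therefore removes little of the bias.

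**Step 4, severe cases in a category of their own.** That category contains no AKI-negative infant, so it adds zero to both numerator and denominator, and the estimate returns to 3.91. A separate category is thus equivalent to exclusion.

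**Step 5, mortality below 100%.** Logistic model of death on AKI and the pooled flag, weighted by expected counts; total 2,162 including the k infants; m = 60; mortality of the k infants 50% to 80%.

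| k | Base 3.91 (14% vs 4%; about 91 AKI deaths) | Base 2.0 (assumed; 3% mortality without AKI; about 38 AKI deaths) |
|---|---|---|
| 5 | 3.99 to 4.06 | 2.11 to 2.19 |
| 10 | 4.05 to 4.18 | 2.20 to 2.35 |
| 20 | 4.15 to 4.39 | 2.35 to 2.61 |

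On the 3.91 base the range runs from 3.99/3.91 = 1.02 to 4.39/3.91 = 1.12, that is +2% to +12%. The shift is larger in the last column because fewer other AKI deaths dilute the added ones. Without the k infants, the 95% interval is 2.8 to 5.5 on the first base and 1.29 to 3.11 on the second.

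**The case against.** The strongest reply is that the plan already deals with this: the covariate is named and the diagnoses are collected. Coding, analysis sets and sensitivity analyses commonly sit in an analysis plan that is not shown. In part this stands. The coding is not stated, so inflation of the adjusted estimate is conditional on pooling. However, the alternative coding only reproduces exclusion (step 4), so stating the exclusion openly loses no information on AKI.

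Other points also stand. The 48 h death exclusion and the 48 h IV-fluid rule remove some of these infants. Their number is unknown. The 2.0 scenario uses an AKI mortality of about 5.8% (38/648.6), whereas every AKI figure in Table 1 is 14% or higher. The model omits the other four named adjusters. In both scenarios the interval excludes 1 before any such infant is added. Keeping these infants with adjustment is a defensible choice for a study meant to be inclusive, and excluding them by kidney function would select on something close to the exposure.

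A reader might infer more than the article supports:
- *That Table 5 removes lethal non-renal anomalies in general and spares only renal ones.* It removes lethal chromosomal anomalies and anencephaly, not every lethal non-renal malformation.
- *That the anencephaly entry shows misclassification.* Listing it under a chromosomal label is clerical; the condition is named explicitly.
- *That all these infants are AKI deaths.* Some may be dialysed, transferred or discharged alive.
- *That discharge creatinine is affected most.* No such effect was calculated, and infants who die are not discharged.

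**Conclusion.** The point holds in limited form. Following Tables 3 and 5 as written, congenital kidney failure in infants surviving past 48 h is counted as stage 3 acute injury, with bias toward the primary hypothesis. Whether the covariate in Table 4 removes that bias depends on coding the article does not give; a pooled covariate leaves most of it.

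The size is modest: about +2% to +12% on Table 1's 14 vs 4 inputs, and from 2.0 to about 2.1-2.6 if AKI mortality is much lower. These figures rest on assumed counts of 5 to 20 infants, 50-80% mortality and 60 mild anomalies. The documents do not support saying that the primary association is produced by these infants or would be reversed without them. A refinement of the analysis set is worth making because it bears directly on whether the association is independent.

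**What to change.** For the Hypothesis 1 and AKI-definition analyses, exclude infants whose recorded structural kidney diagnosis is bilateral absence or non-function from birth. Define the group by the malformation and not by creatinine or dialysis, so that the exclusion does not select on the exposure. Keep the adjustment for the remaining anomalies. Report the excluded infants separately with their number and outcomes, and give the full enrolled cohort as a sensitivity analysis.

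The cost is analysis-set wording, since congenital kidney diagnoses are already collected. The downside is a few infants fewer and a slightly weaker association.
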